## Methods/design

### Design

The proposed research design is a triple-blind (physiotherapist assessor, patient, and treatment provider), randomized, placebo-controlled, parallel-group trial. Participants are randomized to receive either active or sham tDCS for ten sessions of 20 minutes of stimulation over a 2-week period. As illustrated in the flow diagram (Fig. 1), the study includes three evaluation points (pretreatment assessment, post-treatment assessment performed at 2 weeks, and follow-up assessment at 3-months post-treatment). This study protocol was written in accordance with the SPIRIT statement (see Additional file 1 for the completed SPIRIT checklist).

**Fig. 1 Fig1:**
[figure not shown]
Study flow diagram

### Participants

Premenopausal women, ages 18–45 years, suffering from pain during intercourse, are being recruited at the Research Center of the Centre Hospitalier Universitaire de Sherbrooke (CHUS). The eligibility criteria are detailed in Table 1. These criteria were selected to ensure recruitment of a homogenous sample of sexually active women with PVD and were based on previous successful studies [13, 50, 51]. In order to confirm the diagnosis of PVD, the eligibility screening comprises a gynecological assessment performed by a gynecologist from our team, following a standardized protocol. The latter consists of a brief anamnesis and a comprehensive gynecological examination of the vulvar region (clitoris, small lips, interlabial furrow, and vestibule), testing for vaginal infection and sexually transmitted disease, and palpation of the uterus and appendices. This evaluation follows the diagnostic criteria defined by Friedrich [2] and more recently modified by Bergeron et al. [52], namely, (1) pain in the vestibule following touch or an attempted vaginal penetration or (2) acute pain during palpation of the vestibule region with a cotton swab. Interevaluator fidelity of this diagnosis method has been demonstrated [52] and used in several RCTs [13, 53, 54]. Therefore, vulvar pain occurring in the absence of an underlying recognizable disease and provoked spontaneously as a result of physical contact can be classified as PVD [55].

**Table 1 Tab1:** Eligibility criteria

*Inclusion criteria*	*Exclusion criteria*
- Experience moderate to severe pain (minimum of 5/10 on a numerical rating scale (NRS)) in at least 90 % of attempted sexual intercourse - Pain limited to the vestibule during vaginal intercourse and during activities exerting pressure on the vestibule (tampon insertion, tight jeans or pants, cycling, horseback riding) - Presence of provoked vestibulodynia (PVD) for at least 6 months and diagnosed according to the standardized gynecological examination protocol by one of our staff gynecologists - Have a stable sexual partner (sexual activity should include some attempted vaginal penetrations in order to evaluate pain intensity)	- Urogynecological conditions (e.g., active urinary tract or vaginal infection or in the last 3 months, etc.) and other pelvic pathology associated with pelvic pain (e.g., deep dyspareunia) - Have given birth in the last year and breast feeding - Anterior vulvar or vaginal surgery - Refusal to refrain from other treatments 1 month prior to first treatment study until the last 3-month follow-up assessment - Contraindications to transcranial direct-current stimulation (tDCS) (e.g., metallic implant in or near the skull, history of epilepsy, pacemaker) - Previously received tDCS treatment

### Treatments

Participants are randomized to receive ten sessions of either active or sham anodal tDCS over a period of 14 days. tDCS treatments are given once a day, during weekdays (Monday to Friday). Each session lasts 20 minutes [20, 41, 44, 56, 57] and is administered by a research professional experienced in tDCS. The treatment provider is not involved in the patient assessment and is blinded to the treatment allocation by selecting a preset program of the tDCS device (NeuroConn DC stimulator). Two electrodes are applied to the subject’s scalp; the anode is placed over the motor cortex (M1) [58], and the cathode, over the contralateral supraorbital area [20, 41, 44, 57, 58]. For treatment with active tDCS, the intensity of the stimulation is set at 2 mA for the entire duration of the treatment [20, 41, 42, 44, 49, 56]. The parameters used in our study have been tested with many subjects in several different laboratories without side effects [59], apart from a slight itching, tingling, or burning sensation under the electrode during the first seconds of stimulation; discomfort or erythema (skin reddening) under the active electrode; and possible headache in the hours following the treatment. If the stimulation is switched on or off abruptly, the sensation of a short ocular light flash could also be felt by the participant [60]. For subjects receiving sham tDCS (placebo group), the electrodes are positioned in the same areas as the group receiving active stimulation, and the intensity is set at 2 mA for the first 30 seconds of treatment [57], after which the stimulation stops automatically. Just as for active tDCS, participants are advised that a brief tingling sensation may be felt at the beginning of treatment. This method is effective for preserving subject and investigator blinding [61].

In order to report the participants’ adverse events during tDCS treatment, at each treatment session, the treatment provider notes the participants’ side effects, and the subjects are asked to complete a logbook in which they have to report whether they experience any adverse events or pain in the vulvar region, whether related to intercourse or not. Participants also have to record their experienced vulvar pain in the same logbook between the end-of-treatment period and the 2-week post-treatment assessment.

### Recruitment and procedures

Participants are recruited using different promotion strategies: (1) referrals from health professionals (gynecologist, general practitioner, sexologist, psychologist, or physiotherapist); (2) posters and leaflets distributed to women in clinics, universities, professional schools, restaurants, gyms, etc.; (3) Facebook advertisement; and 4) advertisements in local newspapers. Women interested in participating are invited to contact the research coordinator for a detailed explanation of the study and verification of their eligibility. Thereafter, participants undergo a gynecologist’s examination for confirmation of their diagnoses. Once a diagnosis of PVD has been confirmed, the research assistant contacts the participants to confirm their admissibility into the study. Upon doing so, she provides the participants with instructions to follow before the assessment and, then, fixes the appointments. To avoid effects on the vestibular pain sensitivity measurements prior to each assessment, participants will be asked to refrain from smoking and consuming caffeine (coffee, tea, and energy drinks) 4 hours prior to the evaluation [62], to refrain from taking painkillers (Advil®, Motrin®, Tylenol®, etc.) 24 hours before the evaluation [63], and to not have or attempt vaginal intercourse in the 24 hours before the evaluation [64]. After signing the informed consent, the eligible women are invited to undertake a 1-hour pretreatment assessment (baseline) with a physiotherapist specialized in pelvic-floor rehabilitation and pain assessment. During the pretreatment assessment, a structured interview is conducted to collect the patient’s baseline characteristics, and standardized questionnaires are completed. Approximately 30 minutes are required to complete all questionnaires. These questionnaires have been successfully used in our previous studies, without hindering data quality [65]. A vestibular pain sensitivity assessment is also undertaken using the algometer [66]. The participants are then randomized to receive either active or sham tDCS. The same procedures are repeated at the 2-week post-treatment and 3-month follow-up assessments.

### Participant retention and protocol adherence

As for other clinical trials, the greatest challenges pertain to participant retention. Strategies implemented to minimize attrition are as follows: (1) each participant is required to supply her contact information, such as phone number(s) and e-mail address; 2) a research assistant makes sure to remind participants of their appointments, as well as of the importance of their continuous participation; 3) all appointments are flexible to fit in with the participants’ schedule (i.e., early morning, late in the evening, etc.); and 4) participants receive a $20 compensation at three different stages of the study (the assessments) to cover travel expenses and their participation in the study. Adherence to the study protocol is also promoted throughout the trial. The physiotherapist-evaluator has received a standardized training to ensure homogeneity of procedures and reduce bias due to the evaluator. This physiotherapist-evaluator also has access to a detailed written assessment protocol Version 4 (Nov. 2, 2015). The research professional in charge of treatment is not involved in patient assessment and similarly has received proper training for the application of tDCS. The PI also carries out a weekly supervision of the physiotherapist’s and professional’s adherence to protocols. Moreover, the effectiveness of blinding for all physiotherapists and patients is evaluated with a questionnaire. Participants are also asked to abstain from the following PVD-related treatments (i.e., pelvic floor physical therapy, topical lidocaine application, vestibulectomy, and psychotherapeutic and systemic interventions) during their enrollment in the study, and this is monitored at the 2-week post-treatment and 3-month follow-up assessments. In order to avoid missing data, at the end of each assessment, the physiotherapist-evaluator revises all completed questionnaires before the participant leaves.

### Randomization and blinding

After the pretreatment assessment, the participants are randomized into either the active or sham tDCS treatment (ratio 1:1) using permuted blocks of two and four. The allocation is managed by an individual independent from our research team who follows a computer-generated randomization list drawn up by an independent statistician. Participants, investigators, physiotherapist assessors, and the treatment provider remain blinded to group allocation and, therefore, cannot influence the process in any way.

### Outcomes

The Initiative on Methods, Measurement, and Pain Assessment in Clinical Trials (IMMPACT) has recently recommended several outcome domains for use in evaluating the effectiveness of treatment in chronic pain conditions [67]. The current protocol adheres to these recommendations, with outcomes focusing on the multiple dimensions of PVD, such as pain, sexual function, psychological distress, participant ratings of improvement and satisfaction with treatment, and the need to assess the potential impact of treatment on these different dimensions.

#### Primary outcome measure

As recommended by the IMMPACT [67, 68], participants are asked to evaluate their pain during intercourse with an NRS, 0 indicating no pain, and 10, the worst pain ever experienced. This scale has been frequently used in women with PVD [13, 69–71] and shows good reliability, validity, and responsiveness to change [13, 52, 69–71].

#### Secondary outcome measure

##### Pain measurements

Different measurements of pain are recommended by the IMMPACT consensus group in order to evaluate different domains of pain [67, 72]. Ranging from 0 to 74, the McGill-Melzack questionnaire is a 20-item scale allowing the assessment of pain quality (i.e., sensory, affective, and evaluative components). A higher total score is related to more severe pain. This world-renowned questionnaire, studied for its validity, reliability, and responsiveness to change, is commonly used in RCTs [13, 52, 73–78].

Furthermore, the third International Consultation on Sexual Medicine has emphasized the importance of assessing vestibular sensitivity [79]. Our laboratory recently developed an algometer to measure the vulvar pain threshold and tolerance in women with PVD. A gradual pressure (1 to 1000 grams) is applied to three distinct points of the vestibule at the 3, 6, and 9 o’clock positions [80]. Each of these pressure points is applied randomly (e.g., 3,6,9 or 3,9,6 or 6,9,3). During this procedure, each participant is asked to indicate when they start to feel pain (pain threshold) and subsequently the maximal pressure they can tolerate (pain tolerance) (see [66] for more details). Pain intensity is assessed throughout the test using a computerized visual analog scale (CoVas). This assessment has shown good reliability and validity [80].

##### Sexual function measurements

The Female Sexual Function Index (FSFI) is a 19-item multidimensional measure of sexual function evaluating desire, arousal, lubrication, orgasm, satisfaction, and pain. This questionnaire is frequently used in trials involving women with PVD [13, 78]. In addition to good psychometric properties (reliability, internal consistency, and responsiveness to change) [8, 81], normative data are available for this questionnaire, suggesting clinical levels of dysfunctions [82]. Women considered at risk for sexual dysfunction record a FSFI total score of 26 or less [82].

In order to measure the participant’s sexual satisfaction, the Global Measure of Sexual Satisfaction (GMSS) questionnaire is used. This five-item questionnaire has a total score ranging from 5 to 35 and presents good psychometric properties (a high level of internal consistency and test-retest reliability) [83]. Better sexual satisfaction will result in a higher total score. Inclusion of these questionnaires is in line with the recommendations of the IMMPACT consensus group [67] recommending evaluation of the impact of pain on functions.

##### Psychological distress

Many studies have also determined that vulvodynia may even be a source of psychological distress [5, 84]. For these important reasons, different psychological variables are evaluated.

The Pain Catastrophizing Scale (PCS) is a 13-item questionnaire with good reliability, consistency, and responsiveness [8, 85] for evaluating the level of pain catastrophization, a robust predictor of pain and incapacity. The PCS yields a total score (0–52) and three subscale scores assessing rumination (0–16), magnification (0–12), and helplessness (0–24). Research at the University Centre for Research on Pain and Disability indicates that a total PCS score of 30 represents a clinically relevant level of catastrophizing [86].

The State-Trait Anxiety Inventory of Spielberger (STAI-Y) allows discrimination between anxiety as a trait of personality (T-Anxiety) or as an emotional response to a situation (S-Anxiety) [87]. This 40-item questionnaire, in which 20 items are allocated to each of the S-Anxiety and T-Anxiety subscales, has previously been used in women with PVD [78] and has shown a good reliability, consistency, and responsiveness [8, 87]. Responses for the S-anxiety scale assess intensity of current feelings “at this moment” according to the following: (1) not at all, (2) somewhat, (3) moderately so, and (4) very much so. Responses for the T-anxiety scale assess frequency of feelings “in general” according to the following: (1) almost never, (2) sometimes, (3) often, and (4) almost always [88]. Although this questionnaire was not designed or validated to be used with a cut-off score, an earlier Hungarian research used T-anxiety cut-off values as follows: less than 48 indicating no anxiety, 48 to 52 indicating mild or sub-clinical disorder, and higher than 52 indicating significant anxiety [89].

The Beck Depression Inventory questionnaire (BDI) [90] was recommended by Dworkin et al. [67] for assessing depression [91]. This scale has been studied for its reliability and consistency [91] and has also been used in women with PVD [78]. This 21-item questionnaire has a total score ranging from 0 to 63. Higher total scores indicate more severe depressive symptoms. Total score cut-offs for this questionnaire are as follows: 0–9 indicating that a person is not depressed, 10–18 indicating mild-moderate depression, 19–29 indicating moderate-severe depression, and 30–63 signifying severe depression [90].

The Pain Anxiety Symptoms Scale (PASS-20), which evaluates four distinct components of pain-related anxiety (i.e., cognitive, fear, escape/avoidance, and physiological), also shows good psychometric properties [92, 93]. The total score of this 20-item questionnaire ranges from 0 to 100. A higher total score is related to higher levels of pain-related anxiety. Individuals with acute pain presenting a total score exceeding 30 may be at an elevated risk for maladaptive pain cognitions and behaviors promoting chronic pain and disability [94].

##### Satisfaction with treatment and the Patient’s Global Impression of Change

The dimension of patient’s global impression of change (PGIC) is also evaluated [95, 96]. PGIC is a validated questionnaire [97] through which patients self-report selected measures to evaluate perceived reduction in pain using a seven-point scale ranging from “very much improved” to “very much worse” and rate their treatment satisfaction over an 11-point scale that ranges from “completely satisfied” to “completely dissatisfied” in order to assess the clinical significance of the results. Subjective evaluations of pain improvement and treatment satisfaction have previously been evaluated in a randomized trial involving women with PVD [13].

### Ethical aspects

The study has received ethical approval from the comité d’éthique de la recherche en santé chez l’humain du CHUS (14-169). Every potential participant is made aware that there will be no impact on her medical care if she decides not to participate in the study. Women who refuse to participate in the study or who do not fulfill the eligibility criteria are followed by the clinical staff using the most recently proposed vulvodynia guidelines. In order to minimize privacy risks, all participants are identified by an alpha-numeric code. Informed consent is obtained from all participants prior to trial inclusion. This trial is registered at clinicaltrials.gov NCT02543593.

### Statistical considerations

#### Sample size, power, and statistical analysis methods

A total sample size of 34 participants is sufficient to detect a clinical minimal significant difference of 2 [67, 98] on an NRS (unpaired *t* test; α = 0.05; β = 0.80, standard deviation of 2.0) based on the efficacy of tDCS in other painful conditions [57, 99]. This estimation is conservative considering that tDCS in chronic pain demonstrated a mean pain reduction of 4.34 points [40] and that the available case study in a woman with vulvodynia showed a reduction of ten points [49]. To account for potential dropouts, a total of 40 subjects are being recruited. This estimated dropout rate (< 15 %) is based on available studies and our own RCT experience in women with PVD [13, 78, 100].

#### Statistical analyses

Baseline characteristics of the sample will be presented using descriptive statistics. Analyses will be done on the intention-to-treat basis. Parametric test assumptions will be examined and reported. If the data is not normally distributed, nonparametric data will be transformed. The effects of treatment on pain, sexual function and psychological distress will be examined using a mixed linear model for repeated measures. One of the factors will be the GROUP, at two levels (the treatment group receives active tDCS, and the control group, sham tDCS), while the repeated factor will be TIME (baseline, 2-week post-treatment, and 3-month follow-up assessments). Treatment efficacy will be judged on the basis of a significant GROUP*TIME interaction and contrast analysis (i.e., Tukey-Kramer contrasts when using a mixed-model approach) [101] to detect any differences. The difference between the two groups regarding satisfaction and PGIC will also be assessed using a mixed linear model for repeated measures. However, the baseline assessment will not be a repeated time-factor for these analyses. All statistical analyses will be conducted at a level of significance of 0.05. Sensitivity analyses will be conducted to explore the effect of multiple imputation methods to replace missing data. The non-robustness of our results due to missing value will be noted and discussed.

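### The 80% power is stated for one unpaired t test, but efficacy is judged by a GROUP*TIME interaction plus Tukey-Kramer contrasts, and the stated power does not carry over to that rule

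*Protocol article*

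**What the plan says.** The sample-size section (Protocol article, Sample size, power, and statistical analysis methods) states: "A total sample size of 34 participants is sufficient to detect a clinical minimal significant difference of 2" on the pain scale. It names an unpaired t test with "α = 0.05; β = 0.80, standard deviation of 2.0". It continues: "To account for potential dropouts, a total of 40 subjects are being recruited", with an expected dropout rate below 15%.

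The next section (Statistical analyses) specifies a mixed linear model with GROUP at two levels and TIME at three: baseline, 2 weeks post-treatment and 3 months. It sets the decision rule: "Treatment efficacy will be judged on the basis of a significant GROUP*TIME interaction and contrast analysis (i.e., Tukey-Kramer contrasts when using a mixed-model approach". The overall significance level is 0.05. The section does not say which means form the Tukey-Kramer family, or whether one or both follow-ups must show a difference.

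The last paragraph of the Background holds two expectations for the primary outcome. Pain in the active arm should fall from pretreatment to each follow-up, and active should do better than sham at each follow-up.

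**The concern.** The test that justified the sample size is not the test that decides efficacy. The t test compares two means once. The stated rule asks for a significant interaction with 2 degrees of freedom and, joined by *and*, contrasts adjusted for multiplicity. Two group levels and three visits give six cell means. Tukey-Kramer over all six protects 15 pairs, and only two of those compare active with sham at a follow-up.

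The 2-point difference is the protocol's own minimal clinically significant difference. If the rule is materially harder to meet than the t test, a null result would be read as coming from a trial with 80% power when the rule applied had less.

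**Working it through.** **Inputs from the protocol.** Difference 2; SD 2.0; α 0.05 (sidedness not stated; two-sided reproduces the stated N); power 0.80 (printed as β = 0.80, but only power 0.80 gives 34); allocation 1:1; three visits.

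**Assumptions, not in the protocol.** SD 2.0 at each visit; compound symmetry with correlation ρ from 0.3 to 0.7; true group differences of 0 at baseline and 2/2, 2/1 or 2/0 at 2 weeks/3 months. If SD 2.0 is instead the SD of change, then 2·√(2(1−ρ)) = 2 gives ρ = 0.5, which lies inside the grid.

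**1. The plan's own figure.** d = 2/2.0 = 1 and the noncentrality is d·√(n/2). With n = 17 per arm this is √8.5 = 2.92. With 32 df the critical t is 2.04 and power is 0.807. With 16 per arm power is 0.781, so 17 per arm (34) is right. 34/(1 − 0.15) = 40. At 20 per arm power is 0.869. The stated numbers reproduce.

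**2. Interaction alone.** λ = (n/2)·Σ(δₜ − δ̄)² / [σ²(1 − ρ)], F with 2 and 64 df at 17 per arm.
- Pattern 2/2: δ̄ = 4/3, Σ = 16/9 + 4/9 + 4/9 = 2.667. At ρ = 0.5, λ = 8.5 × 2.667/(4 × 0.5) = 11.3 and power is 0.846. Pattern 2/0 has the same sum.
- Pattern 2/1: δ̄ = 1, Σ = 2. At ρ = 0.5, λ = 8.5 × 2/(4 × 0.5) = 8.5 and power is 0.724.

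**3. Six-cell Tukey-Kramer contrast alone.** There are 6 × 5/2 = 15 pairs. The critical |t| is q(0.95; 6, df)/√2, which is 3.03, 2.94 or 2.91 at 32, 64 or 96 df. With noncentrality 2.92, power for active versus sham at 2 weeks is 47–51%, whatever ρ is. The difference detectable with 80% power rises from 2.0 to about 2.6–2.7 points.

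**4. The two-part rule, 17 per arm** (simulation, 20,000 runs per row):

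| ρ | Effect 2 wk/3 mo | Interaction | Interaction and Tukey at 2 wk | Interaction and Tukey at either visit | Interaction and unadjusted 2 wk |
|---|---|---|---|---|---|
| 0.3 | 2/2 | 0.701 | 0.395 | 0.548 | 0.600 |
| 0.3 | 2/1 | 0.566 | 0.370 | 0.381 | 0.519 |
| 0.3 | 2/0 | 0.705 | 0.447 | 0.448 | 0.651 |
| 0.5 | 2/2 | 0.847 | 0.444 | 0.590 | 0.709 |
| 0.5 | 2/1 | 0.725 | 0.423 | 0.430 | 0.638 |
| 0.5 | 2/0 | 0.846 | 0.469 | 0.471 | 0.736 |
| 0.7 | 2/2 | 0.977 | 0.487 | 0.609 | 0.803 |
| 0.7 | 2/1 | 0.918 | 0.476 | 0.478 | 0.770 |
| 0.7 | 2/0 | 0.974 | 0.495 | 0.497 | 0.806 |

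The table uses the compound-symmetry F test. An unstructured interaction test (Hotelling's T² on the two changes from baseline) lowers the interaction column by up to about 2.5 points; at ρ = 0.5 and pattern 2/1, for example, 0.724 becomes 0.700.

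**5. Ranges with the unstructured test**, good to about one percentage point, 17 per arm:
- Interaction and six-cell Tukey at 2 weeks: 37–49% (46–60% at 20 per arm).
- Interaction and six-cell Tukey at either follow-up: 38–61%.
- Interaction and unadjusted contrasts, at 2 weeks only or at either follow-up: 50–87%.
- Interaction alone: 54–97%.

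**The case against.** The case for the plan is substantial. Sizing on a t test and analysing with a repeated-measures model is common, and the sample-size section does not claim its power for the interaction. The contrast family is a detail that an analysis plan may settle. If contrasts are taken between groups within each visit, each family holds two means and Tukey-Kramer is the ordinary t test. The interaction alone exceeds 80% at ρ = 0.5 for two of the three effect patterns. Forty women are recruited, and a mixed model can use partial data, so 17 per arm is near the floor.

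Much of this stands, and it rules out two stronger readings.

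- A reader might infer that the trial simply has 35–50% power and misses a true 2-point effect half the time or more. The protocol does not support that as a flat statement. It needs a Tukey family of all six cells, both parts of the rule required, the 2-week visit alone decisive, and SD 2.0 applying to single scores. None of these is fully fixed in the text. The Tukey step drives most of the loss.
- A reader might infer that 13 of the 15 pairs are irrelevant. They are not. The Background expects the active arm to improve from pretreatment at both follow-ups, so 2 + 2 = 4 pairs bear on stated expectations. It remains true that most pairs are not active versus sham at a follow-up.

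What does not stand is that the mismatch is only an omission. The article states the decision rule itself, and it differs from the test that was powered. The interaction alone is not the stated rule. It has no direction and does not show at which visit active differs from sham. Nor does the protocol's description of its estimate as conservative help: the 4.34-point figure is given as a mean pain reduction, not as a difference from sham, and the ten-point figure is a single case.

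**Conclusion.** The concern holds as a mismatch between the powered test and the decision rule. The figure of 34 is correct for the t test (80.7%), but that power cannot be attributed to the interaction-plus-Tukey rule. With a six-cell Tukey contrast, no scenario examined exceeds about 61% at 34 participants. With contrasts in effect unadjusted, power runs from about 50% to 87%, so some readings reach the stated level and others fall well short. The spread comes from what the text leaves open (family, decisive visit) and from what it does not give (correlation, effect pattern, whether SD 2.0 is for a score or a change). All figures rest on SD 2, compound symmetry and ρ from 0.3 to 0.7.

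**What to change.** For the primary outcome, replace the interaction-plus-Tukey rule with one pre-specified mixed-model contrast: active minus sham pain score at a named primary visit, tested two-sided at 0.05, with its 95% CI and no interaction gate. Test the other follow-up in fixed sequence. Report within-arm changes from pretreatment as secondary estimates with CIs, since the Background asks about them. State whether SD 2.0 refers to the score or to the change, and define the contrast on the same scale. On the plan's inputs this contrast has about 81% power at 34 and 87% at 40, in line with the sample-size section.

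If the present rule is kept, define the contrast family and the decisive visit and restate the power for that rule.

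The cost is one paragraph before unblinding and no extra participants. The downside is that the all-pairs comparisons are no longer confirmatory tests.
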